**3 WHAT ARE THE MEDIATORS OF TREATMENT RESPONSE; I.E. THE UNDERLYING PSYCHOLOGICAL AND BIOLOGICAL MECHANISMS?**

3.1 PROCEDURES AND EQUIPMENT

In order to test emotional processing theory in a preventive treatment context, we will use process data from the randomized trial (research question 1). In each exposure session, the psychologist will ask the patient to give a detailed description of the traumatic event, thereby activating the fear memory. Activation of fear memory elicits an associated fear reaction which we will measure with both the subjective units of distress scale,[^27^](#_ENREF_27) heart rate (measured through standard equipment at the hospital) and skin conductance. The patient is then instructed to hold the fear memory in their mind’s eye and describe it in detail for the psychologist until the fear response associated with the memory has attenuated (also known as “within session habituation”).

We will measure time to habituation and also the individual trajectories for each session i.e. we will assess whether the anxiety habituate in an u-shaped curve as suggested by some research[^28^](#_ENREF_28) or if it has a waxing and waning trajectory as suggested by other studies.[^29^](#_ENREF_29) Process data will be collected each session (in total 3 sessions).

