2.2.3 HOW DO WE ACHIEVE SUCCESSFUL OUTCOME IN TF-CBT?

One final limitation with the Rothbaum et al. study was the lack of investigation of hypothesis driven underlying mechanisms. Revealing the mechanisms of psychological treatments are imperative in order to move the field forward.[^12^](#_ENREF_12)^,^[^13^](#_ENREF_13)^,^[^19^](#_ENREF_19) Thus, the key and also novel area that needs more research is about mediators of treatment response – that is the underlying mechanisms.

TF-CBT is based on “emotional processing theory” which stipulates that, in order to achieve complete emotional processing, the patient needs to a) active the fear memory (initial fear activation), b) stay in the fear memory until the fear subsides (within-session habituation) and c) repeat this procedure until the memory is no longer associated with fear (between-session habituation).[^20^](#_ENREF_20) Although previous studies have shown support for this pathway (i.e. initial fear activation 🡪 within-session habituation 🡪 between-session habituation 🡪 lower PTSD symptoms),[^20^](#_ENREF_20) it has never been tested within a preventive context.

Data on treatment mediators is important because it would provide us with knowledge of how the treatment achieves its effects. For instance, if patients who do not succeed with initial fear activation 🡪 within-session habituation 🡪 between-session habituation would have worse treatment response, it would mean that we could increase the amount of support for these patients and maximize the treatment dose. In addition, research is also lacking on other emotions such as disgust, not-just-right emotions or shame/anger.[^21^](#_ENREF_21) Research about this would not only give us better treatment effects but, even more importantly, it would give us new knowledge about psychological reactions and how to manipulate memory consolidation in the immediate aftermath after experiencing trauma.

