3.2 OUR GENERAL AIM

We see a need for research on TF-CBT as a preventive treatment along as well as to extend this well-defined treatment paradigm to investigate mediators of treatment response and biomarkers, with additional analyses on health economical aspects. As pointed out by the chief director at NIMH in a recent paper in JAMA Psychiatry,[^12^](#_ENREF_12) focus on mediators is especially important as it allows a trial to be informative even if the intervention would not show any incremental effects i.e. we can investigate if we were able to affect the mediator and if the mediator in turn affected the outcome.

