4.1 RESEARCH QUESTIONS

1. Is TF-CBT an effective treatment in preventing the development of PTSD symptoms?
2. Is TF-CBT a cost-effective treatment in preventing the development of PTSD symptoms?
3. What are the mediators of treatment response; i.e. the underlying psychological and biological mechanisms?

Methods

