Participants randomized to TF-CBT will receive a brief 3-session intervention provided within 72 hours after the accident. In this treatment, the patient is instructed to systematically expose him/herself to the fearful memory of the event and stay in this memory until the anxiety has attenuated. By doing this exposure repeated times, the association between the memory and fear response is hypothesized to be gradually extinguished. The placebo group will receive sham treatment i.e. written information about PTSD and how to treat it but without any therapist-guided interventions.

We will measure PTSD symptoms using the Clinician Administered PTSD Scale (CAPS; the gold standard for PTSD assessment) and Posttraumatic Diagnostic Scale,[^22^](#_ENREF_22)^,^[^23^](#_ENREF_23) depression using the Montgomery Åsberg Depression Rating Scale – Self rated (MADRS-S),[^24^](#_ENREF_24) quality of life using the EQ-5D[^25^](#_ENREF_25) and treatment side effects using the Safety Monitoring Uniform Report Form (SMURF)[^26^](#_ENREF_26) at baseline (i.e. before treatment allocation), 2-, 6-, 12-, 24-, 48- and 120 months using blinded assessors. Primary endpoint is set to 6-months after the trauma. Patients unable to come to the clinic for follow-up assessments will be interviewed via telephone or skype.

The primary outcome (significant PTSD symptoms assessed by the CAPS) will be analyzed using risk ratios and numbers-needed-to-treat with 95% confidence intervals. Continuous data will be analyzed in a mixed-effects model adjusting for data attrition (covariance and residual structure will be set based on the best model fit of the data) using intention-to-treat design. Effect sizes for continuous measures will be estimated using Cohen´s *d*. Assessor´s blindness will be also tested (each assessor will guess treatment allocation for each participant and this will be tested in a logistic regression with guess as independent variable and allocation as dependent variable). A flowchart of the treatment study is shown in the attached figure.

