3.2 STATISTICAL ANALYSES

We will then conduct a path analysis and test whether outcome (i.e. PTSD symptoms) is dependent on the following causal steps: initial fear activation 🡪 within session habituation 🡪 between session habituation. As some research has suggested that type of emotional response matter, we will also collect additional data on the primary emotional response (disgust, anger, and not-just-right emotions) on disgust, anger and not-just-right emotions factor variables in a predictor model.

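### Fear activation and habituation are measured only in TF-CBT sessions, so the trial cannot show that treatment changed them relative to control; question 3 is a within-arm association

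*Protocol*

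**What the plan says.** Protocol 4.1 (Research questions) puts the third question as "What are the mediators of treatment response; i.e. the underlying psychological and biological mechanisms". Introduction 2.2.3 says of mediator data that "it would provide us with knowledge of how the treatment achieves its effects". Introduction 3.2 (Our general aim) goes further. It argues that a trial can be informative even without an incremental effect, because "we can investigate if we were able to affect the mediator and if the mediator in turn affected the outcome".

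The measurements are described in Methods 3.1: "In each exposure session, the psychologist will ask the patient to give a detailed description of the traumatic event". The next step is "Activation of fear memory elicits an associated fear reaction which we will measure with both the subjective units of distress scale", together with heart rate and skin conductance. Time to habituation and the trajectory within each session are also recorded. The schedule is "Process data will be collected each session (in total 3 sessions".

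Methods 1.1 gives the control arm "written information about PTSD and how to treat it but without any therapist-guided interventions". The instruments listed there for baseline and for follow-up from 2 to 120 months are the CAPS, the Posttraumatic Diagnostic Scale (PDS), the MADRS-S, the EQ-5D and the SMURF.

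The analysis in Methods 3.2 is a path analysis to "test whether outcome (i.e. PTSD symptoms) is dependent on the following causal steps", running from initial fear activation through within-session to between-session habituation. It names no treatment-arm term. The section on societal implications later calls this work a mediation analysis.

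**The concern.** A claim that treatment worked by changing a mediator needs two links: treatment changes the mediator, and the mediator changes the outcome. Randomisation protects the first link, but only if the mediator is observed in both arms. Here it is observed in one.

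What is at stake is the conclusion drawn from question 3. If the path analysis is reported as a set of causal steps or as mediation, readers will take it to explain the between-arm effect. Patients who habituate well in session may simply be those who would have recovered anyway, and Introduction 2.2.1 itself expects a sizeable share of spontaneous recovery. Introduction 2.2.3 foresees using the findings to decide which patients receive more support, so a causal misreading would have practical consequences. Introduction 3.2 also relies on the mediator work to give the trial value if efficacy is null, and in that case the comparison with control would be missing.

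**Working it through.** **Sample size.** Methods 1.1 gives 352 patients, 176 per arm, for d = 0.3, alpha 0.05 and 80% power. The normal approximation is n per arm = 2 × (1.960 + 0.842)² / 0.3² = 2 × 7.849 / 0.09 = 174.4, so 175 per arm and 350 in total. The t-based solution is 175.4, so 176 per arm and 352 in total. The stated figure reproduces with a two-sided test. It concerns the between-group comparison and nothing below changes it.

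**Where mediator values can exist.**

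| Arm | Sessions (Methods 1.1) | Patients | Patients with fear-activation or habituation data |
|---|---|---|---|
| TF-CBT | 3 | 176 | at most 176 |
| Control | none | 176 | 0 |

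The maximum is 176 / 352 = 50% of the randomised sample. It is a maximum because a between-session value needs at least two attended sessions.

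**What can be estimated.** Write T for arm, M for the mediator and Y for later PTSD symptoms.

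- The treatment-to-mediator path is a = E[M | T = 1] − E[M | T = 0]. The second term has no observations, so a cannot be estimated.
- The indirect effect is a × b, where b is the mediator-to-outcome path. Without a, neither this product nor the proportion mediated can be estimated.
- Among patients with an observed M, T is always 1. The design matrix [intercept, T, M] then has rank 2 of 3 (checked numerically with 176 patients per arm), so a treatment term and an intercept cannot be separated.
- The slope of Y on M within the TF-CBT arm can be estimated. This is what the path analysis in Methods 3.2 can deliver.

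**What the within-arm slope means.** Two data-generating scenarios were compared, with M and Y scaled to variance 1.

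- Scenario A: M lowers Y directly, Y = −0.3 M + noise. The slope is −0.3.
- Scenario B: M has no effect on Y. A shared prognostic factor U enters M with coefficient √0.3 and Y with coefficient −√0.3. The slope is cov(M, Y) / var(M) = −0.3 / 1 = −0.3.

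Simulation with 400,000 draws gave −0.300 for A and −0.299 for B. The coefficients are illustrative and do not come from the protocol. The point is that a within-arm slope alone does not separate the two scenarios.

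**The case against.** The best defence is that Methods 3.2 never promises a between-arm mediation model. It names a path from activation to habituation to outcome, with no arm term and no proportion mediated. Introduction 2.2.3 gives that path a narrower use: whether patients who do not activate or habituate respond worse. Within-arm data address this, as association. This stands. A reader might infer that question 3 cannot be answered at all or that the path analysis cannot be run, and the protocol does not support either inference.

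A second defence concerns Introduction 3.2. In a null trial the data would still show whether habituation occurred in treated patients and whether it tracked outcome. This also stands, so the statement is not empty. What is missing is whether treatment changed habituation relative to control, and that is what affecting the mediator means in a randomised comparison.

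Third, confounding of mediator and outcome is not caused by the missing control data. Measuring the mediator in both arms would identify the first link, but the second would remain non-randomised. This is correct. The simulation therefore bears on the causal wording, while the missing control arm bears on the treatment-to-mediator path.

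Fourth, halving the available sample might be read as a power shortfall. The protocol sets no precision target for question 3, so there is no stated benchmark to fall short of.

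The abstract lists process data among the trial's measures without naming an arm, but the Methods provide for no collection in controls. The defence does not remove the conflict between what is collected and the wording of Introduction 3.2, Methods 3.2 and the societal implications.

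**Conclusion.** The point holds as a mismatch between the data to be collected and the claim attached to them. There are no control-arm mediator values. The treatment-to-mediator path and the indirect effect are therefore not estimable, and the trial cannot show whether treatment affected the mediator relative to control. What remains is a non-randomised process-outcome association in at most 176 TF-CBT patients.

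This rests on reading Methods 1.1 and 3.1 as the full account of what is measured in each arm. A statistical analysis plan could reword the analysis but could not supply control-arm measurements that are never taken.

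A reader might infer that the defect threatens the trial's main result. It does not: the primary endpoint, its analysis and the sample size of 352 do not depend on question 3. The wording is wrong as it stands and should be corrected, but this is not a must-fix for the primary question.

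**What to change.** Restate research question 3 and Methods 3.2 as an exploratory process-outcome analysis within the TF-CBT arm, with at most 176 patients. Adjust it for severity measured before allocation (CAPS, PDS and MADRS-S, all already collected at baseline), and report the result as association. Adjustment reduces prognostic confounding but does not remove it, and the text should say so.

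Replace the causal-steps wording in Methods 3.2, the mediation-analysis wording under societal implications and the statement in Introduction 3.2 with text limited to that analysis: whether activation and habituation were seen in treated patients, and whether they were associated with later symptoms.

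The cost is a protocol wording change with no new data. The downside is a more modest claim for question 3. A between-arm mediator claim would need a comparable measure taken in both arms before the outcome, which rewording cannot provide.

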3.2 STATISTICAL ANALYSES

We will then conduct a path analysis and test whether outcome (i.e. PTSD symptoms) is dependent on the following causal steps: initial fear activation 🡪 within session habituation 🡪 between session habituation. As some research has suggested that type of emotional response matter, we will also collect additional data on the primary emotional response (disgust, anger, and not-just-right emotions) on disgust, anger and not-just-right emotions factor variables in a predictor model.

# Ethical considerations

Patients will receive both written and verbal information about the study. Participation is voluntarily. It will be possible to participate in the treatment trial but not in the genetic investigation. The collaborator ([name]) has research experience of informed consent in an Emergency Department, and procedures for working with the medical team more broadly.

Source data will be quality monitored by an independent party (KTA) according to the Helsinki Declaration. We will set the quality control as equal to a pharmacological trial.

We will also conduct at least three interim analyses during treatment. The reason for this is to monitor potential side effects associated with treatment such as worsening of symptoms. The interim analyses will be conducted by KTA and handled according to good clinical practice.[^30^](#_ENREF_30) If TF-CBT would be shown to cause any serious side effects, we will make an assessment together with external experts if the study should needs to be stopped beforehand. This is an important issue from an ethical perspective as one psychological intervention for PTSD (i.e. “Debriefing”) has actually shown worsening of symptoms compared to treatment-as-usual.[^17^](#_ENREF_17) However, given the positive Rothbaum trial this is unlikely for this new intervention.

# Working plan

Preparation for the study

[name] (planned PhD student of this project) has the last quarter established routines at the emergency department and shown that it is feasible to implement TF-CBT within this context. [name] is the only certified TF-CBT trainer in Europe. [name] (collaborator) has just completed an RCT in an emergency department of a different intervention (a computer game) demonstrating the feasibility of recruiting patient soon after trauma, working within a busy hospital setting and recruitment rates needed for the successful completion of this trial in the time frame. We have also extensive collaboration with leading figures in the trauma clinic at Karolinska University Hospital (see below). The study is sanctioned also by Psykologkliniken who will be the main sponsor of this study and enable infra structure, personnel etc. We have also translated and validated the PTSD outcome questionnaires and interviews for a Swedish population. Thus, preliminary results from Rothbaum et al. suggest that TF-CBT can prevent PTSD and our research group has the resources and competence to investigate this in more detail.

Time plan

- 2015 Consolidation of the treatment manual and establishing routines at Traumacentrum Karolinska
- 2016-2017 Recruitment, treatment with TF-CBT
- 2017-2019 Follow-up assessments. Primary endpoint completed.
- 2019- Write papers
- 2020- Publish papers
- 2020🡪 Long term follow-up assessments (not within the scope of this application)

# Scientific implications

This project holds important scientific implications:

First, there is to date only one early stage randomized controlled trial in the USA showing that PTSD can be prevented through TF-CBT. This current study is unique in providing an adequately powered test of the hypothesis using a larger sample size, allowing longer-term follow-up assessments, as well as appropriate monitoring of treatment side effects. In addition, the health economical analyses will reveal how much the society needs to pay for one non-case of PTSD. This study is therefore set to be the definitive trail internationally.

Second, a unique aspect of this clinical research study is that we will examine the underlying mechanisms of the treatment, drawing on work in basic neuroscience and cognitive theory. The intervention is hypothesized to modify the trauma memory, and thus to prevent the development of PTSD symptoms, before any major memory consolidation has taken place (i.e. sleep on night one[^31^](#_ENREF_31)) which would otherwise cement the traumatic memories in a maladaptive way. It would therefore be of great scientific value to see if the stipulated effect of the emotional processing theory, which TF-CBT draws upon, applies within this preventive context in a non-psychiatric sample. We will also investigate the role of different emotions and their consequences in treatment outcome. There is a lot of research on fear extinction but, as many other emotions are involved in PTSD as well as other mental disorders, the next step would also to investigate the role of disgust, shame etc. and see if these emotions follow the same path as fear extinction. Research about emotional memory consolidation and treatment mediators would give us highly valuable information both about the etiology of PTSD, and also information on how to treat PTSD in the most effective way with psychological interventions. If we know how our treatment works optimally, we can implement additional instruments and procedures that ensure that we activate the working mechanisms in this treatment. Critically, this study will also be able to demonstrate whether treatment success (or failure) is contingent on the hypothesized mechanisms. Therefore this study will be among the first to link the basic laboratory work on memory consolidation to an applied real world setting.

These additional aspects of the study are useful step in tailoring preventative treatments, will also add value to the study, regardless of whether the treatment if successful or not (which in itself is a critical question to test) contributing both the basic and clinical science base.

# Societal implications

In the last decade, both the Swedish Government and the National Board of Health have underscored the importance of using a preventive health care approach.[^32^](#_ENREF_32)^,^[^33^](#_ENREF_33) PTSD is a major public health concern with long-term sequelae, and given the signiﬁcant public health impact of PTSD, there is a need for research on brief and cost-effective interventions that are easy to disseminate.

If TF-CBT would be shown effective, it would mean that the health care system could access and implement a new and brief intervention to the treatment armament and potentially “vaccinate” many trauma patients from developing PTSD. The cost-effectiveness aspect of the study will also provide us with important data whether TF-CBT also can decrease the burden on the social welfare system as well as psychiatry and addiction care. Thus, this project also holds important precision prevention features, similar to what has been done in cancer-, heart disease- or diabetes- research,[^12^](#_ENREF_12)^,^[^13^](#_ENREF_13) moving this for the first time in Sweden to psychological treatment research and mental health. Lastly, the data from the mediation analysis would provide us with better knowledge what to focus on in psychological treatment, hence potentially improve these interventions and thereby minimize treatment failures for many patients.

The prospect of being able to prevent PTSD by means of a psychological intervention poses great challenges, but the rewards are of immense importance: not only to the thousands of people in Sweden who every year are victims of road traffic accidents or interpersonal violence, but also to the millions of people worldwide who will experience inevitable future traumatic events.

Collaborations:

**[name]**, associate professor at Emory University Atlanta USA, is an external consultant in the current project. [name] is one of the top leading researchers on translational models of fear extinction, and was also one of the main authors behind the previous RCT on TF-CBT conducted in Atlanta, USA.[^16^](#_ENREF_16) We have previously worked with [name] in a randomized pharmacotrial with great success. More info at <[name]>. [name] will serve the function as an external consultant in the current project.

